## Abstract

(1) Background: Human polycystic ovary/ovarian syndrome (PCOS) is linked to endocrine, metabolic, and psychological complications. We propose a randomized controlled pilot study for an acupuncture protocol regarding the management of PCOS symptoms based on TCM diagnosis; (2) Methods: We will randomly allocate 120 women diagnosed with PCOS into two groups. The study group will be treated with acupuncture for points known to act upon the autonomous regulation of the hormonal, metabolic and emotional components. (3) Results and Conclusions: We expect to provide evidence of high methodological quality related to the effects and safety of an acupuncture protocol based on the perspective of a TCM diagnostic.

## 1. Introduction

Polycystic ovary/ovarian syndrome (PCOS) is considered the most frequent endocrine pathophysiology among women of fertile age, displaying a prevalence between 5 and 15% relative to the clinical diagnostic criteria [1]. Azziz et al., 2004, estimated an annual cost of about 4.37 billion dollars spent in identification and management of the PCOS condition in the USA, which demonstrates the importance of investing in solutions for this condition’s symptoms. With a still unidentified origin, the diagnostic of this syndrome is always made by exclusion of conditions that mimic the phenotypes [2]. In 2003, the European Society for Human Reproduction and Embryology (ESHRE) and the American Society for Reproductive Medicine (ASRM) reformulated the diagnosis criteria of PCOS. Two out of the following three criteria should be present to confirm the syndrome: oligo/anovulation, androgen excess, and the confirmation of polycystic ovarian morphology by imaging. These are designed as Rotterdam criteria, and from them, it is possible to identify four distinct phenotypes of PCOS (Table 1). PCOS has been strongly associated with alteration in the autonomic nervous system: namely, increased sympathetic nervous activity [3]. Endocrine and metabolic implications of the syndrome reflect a high comorbidity [4] within three major aspects: hyperandrogenism [5,6,7,8] and reproductive issues [9,10,11,12], metabolic [13,14,15,16,17,18], and mental or emotional [19,20,21,22,23,24,25,26]. Different clinical strategies have been designed for PCOS management according to international guidelines [11,27,28,29]. However, allopathic therapies have shown several unpleasant secondary effects, which motivate PCOS women to search for complementary medicines such as traditional Chinese medicine (TCM). Among the TCM therapeutics, acupuncture has been used as therapy or co-therapy to improve the comorbidity’s symptoms affecting women with this condition. Diverse studies using low frequency electroacupuncture (EA), alone [30,31] or in combination with exercise to modulate the sympathetic system, concluded that acupuncture seems to regulate the hypersecretion of androgens, improving both the reproductive and endocrine metabolic functional state [32]. Acupuncture has also been used, alone or in combination with clomiphene, to ameliorate the disorder of subfertility in PCOS patients [33,34]. With respect to psychological balance, acupuncture studies were designed to relieve anxiety and depression in PCOS patients [35]. Acupuncture therapy is thought to have a positive impact on the treatment of PCOS through the following mechanisms: sympathetic output modulation through spinal reflexes [36]; modulation of hypothalamic–pituitary–adrenal (HPA) and hypothalamic–pituitary–gonadal (HPG) axes through the increase of β-endorphin secretion [37,38,39,40,41,42]; and influencing insulin sensitivity or resistance through functional balance of the insulin signaling pathways [43]. PCOS in TCM is considered a complex combination of different factors that end up in blockage of the communication between the Penetrating (Chong Mai) and Conception (Ren Mai) vessels, compromising the female’s fertility and reproductive cycle normalization, with or without association to pathogenic heat and phlegm (Lyttleton, 2013). Usually, patients present a tendency to a kidney Yang and/or Yin deficiency, possibly associated to a Qi deficiency in spleen or lung, hence leading to a weakened Shen in the long run. On the other hand, we can have a scenario where kidney Yang deficiency may be associated to Xue stasis leading to cardiac phlegm/dampness in the long run, and, therefore, a disturbed Shen. Main pathogenic factors generating this condition may be stress/overworking, emotional origin (sadness, fear, or excessive worry), cold or phlegm/dampness. According to Maciocia, the kidney is the internal organ most closely associated to the ability to conceive, therefore kidney deficiency is the pattern most commonly found among gynecological pathologies. Kidney deficiency can be due to kidney Yin and/or kidney Yang deficiency. The same author referenced that the overlap of blood and kidney deficiency are quite common due to the relation of kidneys/uterus/blood/Penetrating vessel (Chong Mai). The Penetrating vessel supplies blood to the uterus; however, this supply is also managed by the provision of blood from the liver, the internal organ that stores the blood. So, this liver-blood is key for a healthy menstrual function. Not to mention that, according to the Five Element Theory, Water is the mother of Wood, meaning that the kidney organ is the mother of the liver which is consensual with the relation between essence and blood: kidneys store Jing/essence and the liver stores blood; hence, essence is the mother of the blood. Most published studies of acupuncture in PCOS are concerned with anovulatory cycles and sub/infertility, addressed in TCM as TianGui disorder [44], which is the disorder for which most women seek for help in complementary medicine. However, many women also search for the treatment of symptoms associated with hyperandrogenism either for aesthetic reason, such as acne and alopecia, or for derived comorbidities such as overweight, insulin resistance, diabetes type II, and others. Recent analysis of obstetric outcomes in TCM syndromes showed that possibly more than the usual two distinctions between kidney deficiency and phlegm-dampness and/or blood stasis may be found in women diagnosed with PCOS. Wang et al. (2017) made a secondary analysis of the results of the RCT of Wu et al., 2016, and concluded that it is possible to identify four TCM phenotypes that could be correlated with the four phenotypes according to the Rotterdam criteria (Table 1). According to the author, these four TCM phenotypes would be: “kidney deficiency and liver stasis” (40.29%), “spleen deficiency and phlegm stasis” (32.27%), “phlegm stasis and blood stasis” (16.55%), and “kidney deficiency and blood stasis” (10.89%)—to help in understanding the syndromes according to TCM, we can leave a quick definition of these patterns regarding the reproductive function. According to Lyttleton, kidney deficiency can be translated in symptoms such as in the study, where kidney deficiency with liver stasis patients showed a tendency to have psychological or mental problems [45]. Spleen deficiency and phlegm stasis patients presented metabolic abnormalities, including higher body weights, body mass index, waist and hip circumferences, systolic blood pressure, free androgen index, triglycerides, alanine transaminase, and occurrence of metabolism syndrome. Patients with phlegm and blood stasis had higher free testosterone and insulin, and patients with kidney deficiency with blood stasis presented a more severe reproductive disorder including higher luteinizing hormone and the ratio of luteinizing hormone to follicle stimulation hormone. In general, patterns derived from kidney deficiency demonstrated an association with psychological or mental problems, while patterns associated to phlegm syndrome had more severe glucolipid metabolic abnormalities.

According to what was mentioned before, it would be an important contribution for PCOS patient treatment to perform an acupuncture randomized controlled trial according to TCM diagnosis of the condition. In this sense, we made a revision of the literature produced during the last five years on TCM PCOS management (data not shown), and we found important limitations that we will try to overcome with the proposed study. So, we designed an acupuncture RCT study according to the TCM pathomechanism associated with PCOS proposed by Lyttleton (2013). According to this proposed mechanism, impairment of the Conception and Governing vessels is a common denominator to gynecological problems. Moreover, Conception and Governing vessel deficiencies are closely related to kidney deficiency. Most women diagnosed with PCOS according to the Rotterdam criteria show Phenotype A or 1 and Phenotype C or 3 (Table 1), which are both characterized by polycystic ovary morphology plus ovulatory disfunction, and in the case of the first phenotype, it is also considered that the diagnosis will show the presence of signs and symptoms of hyperandrogenism. Attending to the common denominator of ovulatory disfunction, we can consider the TCM pattern of kidney deficiency in both main groups, because when the kidney Yin is compromised, the glands and hormonal regulation of the body is considered to be compromised as well—the kidney is the internal organ in TCM associated with the reproductive capacity as well to the development of the fetus. On the other hand, the polycystic ovary morphology can be related to not only kidney deficiency but also to stagnant blood and liver Qi. If liver Qi is stagnant for too long, the function of the body where the liver channel travels might be altered/blocked so we can find pain and difficulty in the egg release in the ovaries as well as the formation of cysts for anovulation. This cyst formation is considered to be the presence of phlegm-dampness in the reproductive system. So, thereby, that is the reasoning behind the kidney deficiency + phlegm-dampness. According to TCM, Qi (energy) is considered the mother of the Xue (blood), meaning that if the flow of qi is compromised in the body so is the flow of Xue. The kidney Yang deficiency in some women will manifest as a deficient qi and, to some degree, it will compromise blood microcirculation (designated as Xue stasis in TCM) affecting the function of the internal organ heart in TCM, leading to Heart Fire. This Heart Fire not only is manifested by anxiety but also causes or worsens the pre-existence of kidney deficiency, especially kidney Yin deficiency. Thus, we justified the simple division in the second branch of patterns: kidney deficiency + blood stasis. Blood stasis might be also concomitant with the presence of blood deficiency (either for blood loss, unhealthy dietetic habits, overwork, or even as ethiological—part of the constitution of that female individual). Normally, when the level of blood is low, also the flow or its circulation is often slower. According to Maciocia, to address the Extraordinary vessels is absolutely essential in the treatment of PCOS for the reason that it will allow to resolve the dampness-phlegm from the uterus and to tonify the kidneys (and, therefore, regulate the hormones). In this way, from tonifying the kidney, we expect a better functioning of the Conception vessel, moving stagnant Qi and contributing to unblocking uterus blood stasis—present in kidney deficiency associated with blood stasis syndrome and to deblock phlegm-dampness, present in kidney deficiency associated with phlegm-dampness syndrome. Thus, for women diagnosed with kidney deficiency associated with phlegm-dampness syndrome and/or with the main symptoms of spleen deficiency or liver stasis, we propose Protocol A of acupuncture (Table A1 and Figure 1a), and for women diagnosed with kidney deficiency with the main symptoms of blood stasis (with or without phlegm stasis), we propose Protocol B (Table A1 and Figure 1b).

## 2. Materials and Methods

### 2.1. Study Design

We propose a randomized, sham-controlled, single-blinded trial that aims to ameliorate PCOS symptoms, namely, clinical and biochemical hyperandrogenism, ovulation rate, glucolipidic profile, IR, metabolic syndrome, and mental health-related parameters such as anxiety, depression, and quality of life in women diagnosed with this condition. The proposed study trial follows the SPIRIT guidelines and checklist.

### 2.2. Recruitment, Participants, and Randomization

We propose a two-armed pilot study comparing the effects of active acupuncture (SG) with sham acupuncture (CG). The flow chart of the study design is shown in Figure 2. The sample will be 120 women, divided in two main groups according to the TCM diagnosis: Group A (*n* = 60): kidney deficiency associated with phlegm-dampness syndrome and/or spleen deficiency or liver stasis and group B (*n* = 60): kidney deficiency with main symptoms of blood stasis. Each group should have a total of 60 participants to achieve statistical difference in the case of 20% withdrawal of the participants [34]. Participants will be recruited directly from the family doctor and/or hospital specialty of gynecology/endocrinology. Each medical practitioner will refer patients with PCOS diagnostic aged between 18 and 59 y.o. with main symptoms of metabolic imbalance and women between 18 and 40 y.o. with main symptoms of hyperandrogenism and fertility issues to the principal investigator to be later recruited by telephone interview. Patients who show interest in participating will first be prescreened and recorded by an intake to verify that they meet basic inclusion criteria. All questions about the study, as well as the written informed consent, will be explained in detail. The goal of the screening visit will be to confirm a diagnosis of PCOS and to exclude major medical illnesses. These tests will aim to confirm the western and TCM diagnostic. Women diagnosed with kidney deficiency associated with phlegm-dampness will be randomly allocated by a computer program in a 1:1 ratio to two groups of 30 individuals each, one will be the study group (SGA) submitted to active acupuncture, and the other will be the control group submitted to sham acupuncture (CGA). The same procedure design will be applied to the 60 women diagnosed with kidney deficiency associated with blood stasis (SGB and CGB). All baseline and follow-up measures should be obtained on a single day. However, questionnaires may be spread between the screening and the baseline visit (Table 2).

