In short, the combination of Gǔangyúan REN-4 with Tàixī KID-3 and Tàichōng LIV-3, both Earth points, contributes to treat kidney deficiency and tonify liver blood, soothing the liver’s Yang hyperactivity, and rooting the Shen, thus, calming emotions [49]. The sedation of Bàihuì DU-20 may add to the relief of anxiety. On the other hand, Zhōngjí REN-3 and Zhōngwăn REN-12 will also contribute to moving the stagnated Qi associated with phlegm-dampness syndrome. Stimulating points in the lower Triple Burner, namely, Shēnmài BL-62 and Si3 Hòuxī SI-3, we expect an improvement of issues related to food, fluids, blood stasis, accumulated phlegm, and stagnant emotions derived from kidney deficiency associated with phlegm-dampness syndrome. The Qi stagnation observed in these patients usually leads to an imbalance in the transforming function of the Earth element for which Tiānshū ST-25 and Sānyīnjiāo SP-6 may help to restore the Qi and Xue circulation for a general improvement of homeostasis [45]. In women presenting blood stasis, the Conception–Governor vessel circulation is prone to an imbalance that leads to frequent amenorrhea and fertility issues. For that, we suggest regulating the Conception vessel to promote a healthy reproductive cycle by opening Ren Mai and restoring harmony by pairing the Luo points Zhàohăi KID-6 with right Lièquè LU-7 and right Nèiguān P-6 with left Gōngsūn SP-4 to regulate the Conception, Governing, and Penetrating vessels [49]. We would also add Tiānshū ST-25, Guīlái ST-29, and Yīlíngqúan SP-9 to stabilize and harmonize the Earth movement, nourishing blood and eliminate stasis with the spleen’s reinforcement [45]. Based on the characteristics of the referred points, we designed two protocols: Protocol A includes: Zhōngjí REN-3 (dispel), Gǔangyúan REN-4 (tonify), Zhōngwăn REN-12 (dispel), and Tiānshū ST-25 bilaterally (dispel) and Sānyīnjiāo SP-6 bilaterally (tonify). Needles will also be placed in extra segmental acupuncture points: Bàihui DU-20 (sedation), Tàichōng LIV-3 (dispel), Tàixī KID-3 (tonify), Shēnmài BL-62 (dispel), and Hòuxī SI-3 (tonify). In total, 14 needles will be placed (Table A1, and Figure 1a). Protocol B: consists of 16 needles placed in segmental abdominal points; Zhōngjí REN-3 (dispel), Gǔangyúan REN-4 (tonify), Qìhăi REN-6 (tonify), Tiānshū ST-25 (dispel), Guīlái ST-29 (dispel), bilaterally, and extra segmental points: Yīlíngqúan SP-9 bilaterally (tonify), Nèiguān P-6, left Gōngsūn SP-4 (tonify), left Zhàohăi KID-6 (tonify), Tàixī KID-3 (tonify bilaterally), right Lièquè LU-7 (tonify), and Bàihuì DU-20 (sedate) (Table A1 and Figure 1b). Needles and insertion: disposable 25 **×** 25 needle will be used. Insertion depth will be 15–35 mm into skeletal muscle or fibrous tissue. The depth of needle insertion could vary according to the location depth of the acupoint between patients depending on body mass index (BMI), as depth should be enough to reach muscle/fibrous tissue. Stimulation: When needles are inserted, they will be stimulated by manual rotation circa 180 degrees back and forth to evoke tingling sensation—so called de Qi—reflecting activation of sensory afferents. As soon as Qi sensation is reached, the needle should not hurt or cause any pain or discomfort. After 10 min, needles will be stimulated manually. This should be repeated after 20 min and again after 30 min. Two sets of acupuncture points will be used according to the symptoms of each study group.

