### 4.3. What We Expect with the Trial

With the proposed trial, we expect to validate an acupuncture protocol in terms of efficacy and safety that can be a useful tool in the management of symptoms associated with PCOS. With this study design, we expect to find evidence that active acupuncture can be more helpful for promoting follicular development, adjusting the menstrual cycle, and increasing ovulation rate in women with PCOS than sham acupuncture and the long-term effect of the treatment. After active acupuncture treatment, it is expected to find a relative reduction of the biomarkers when comparing to baseline values regarding LH, LH/FSH, total free testosterone, androstenedione, estradiol, BMI, waist circumference, WRH, modified Ferriman–Gallwey score, and Ludwig visual score. We expect an improvement of biochemical hyperandrogenism and HPG axis imbalance, a decrease of androstenedione and sex-hormone-binding globulin, besides the expected decrease in the levels of LH, LH/FSH ratio, total testosterone, estradiol, and on the scoring of the modified Ferriman–Gallwey and Ludwig scales. We expect a possible increase in FSH, progesterone, and the ovulation rate after active acupuncture. With respect to secondary outcomes, we will explore the effect of the acupuncture treatment on metabolic symptoms and expect to describe the metabolic profile of each phenotype before and after the respective treatment. We will adopt international measures as a gold standard for assessing the metabolic status criteria. Besides HOMA-IR improvement, we expect to find a positive correlation between active acupuncture and reduction of the levels of triglycerides, total cholesterol, LDL-C, LDL/HDL, fasting glucose, fasting insulin, and serum insulin and an overview improvement of the metabolic syndrome development. In addition to that, we will try to understand the efficacy of the treatment on exploratory parameters related to the quality of life of the patient, many times disregarded in this type of treatment, especially in anxiety and depression scoring. In this regard, we expect to find a better scoring in the respective questionnaires (reduction in the scoring points of Zung Depression and Anxiety scales and a gain of points in the SF-36 questionnaire) after active acupuncture intervention, particularly in phenotypes where liver fire associated with kidney deficiency originates a lack of mental presence or easy loss of temper. With the results of the study, we also expect to obtain evidence on the possible correlation of phenotypes based on the Rotterdam criteria and those based on the TCM diagnosis proposed by Wang et al., 2017.

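### The declared two-arm contrast averages two different needle protocols, so it cannot by itself support a claim about either one

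*Protocol article*

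**What the plan says.** The Abstract describes the allocation this way: "We will randomly allocate 120 women diagnosed with PCOS into two groups". Section 2.2 gives the comparison as "We propose a two-armed pilot study comparing the effects of active acupuncture (SG) with sham acupuncture (CG".

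The same section then sets out a four-cell layout. The 120 women are "divided in two main groups according to the TCM diagnosis", 60 in each. Women in the phlegm-dampness group "will be randomly allocated by a computer program in a 1:1 ratio to two groups of 30 individuals each", giving SGA and CGA. For the other group: "The same procedure design will be applied to the 60 women diagnosed with kidney deficiency associated with blood stasis (SGB and CGB".

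The active treatment differs between the two diagnosis groups. Section 2.5.1 says "Based on the characteristics of the referred points, we designed two protocols", and Table A1 lists the points for each. The sham procedure is the same in both groups.

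Section 3.3 names chi-square tests, two-sample t-tests or Wilcoxon tests, and an analysis of variance between and within groups. It does not say which groups are contrasted. Stratified analysis is mentioned only as a conditional step against confounding, with no stratum named.

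The intended conclusion is in the singular. Section 4.3 says "we expect to validate an acupuncture protocol in terms of efficacy and safety", and the Abstract expects evidence on the "effects and safety of an acupuncture protocol based on the perspective of a TCM diagnostic".

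**The concern.** What section 2.2 calls active acupuncture is two treatments, each given to a different kind of patient. An SG versus CG difference is a weighted average of the effect of Protocol A in group A and the effect of Protocol B in group B. With equal stratum sizes the weights are one half each.

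That average is a legitimate quantity, but it is not the effect of a protocol, and section 4.3 wants to validate one. If only one protocol works, a significant average could be taken as support for the other as well. A non-significant average could lead to a working protocol being dismissed.

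There is also a limit on the conclusion. Every active woman receives the points assigned to her own diagnosis. The trial can compare that package with sham, but it cannot show what choosing points by diagnosis adds.

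**Working it through.** **1. Are the two active treatments really different?** Counted from Table A1:

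- Protocol A: REN-3 (1), REN-4 (1), REN-12 (1), SP-6 (2), ST-25 (2), LIV-3 (2), KID-3 (2), DU-20 (1), BL-62 (1), SI-3 (1). The sum is 14, as section 2.5.1 states.
- Protocol B: REN-3 (1), REN-4 (1), REN-6 (1), SP-9 (2), ST-25 (2), ST-29 (2), KID-3 (2), KID-6 (1), LU-7 (1), DU-20 (1), P-6 (1), SP-4 (1). The sum is 16, as stated.
- Common to both: REN-3 (1), REN-4 (1), ST-25 (2), KID-3 (2), DU-20 (1), which makes 7.

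So 7 of 14 needles in A and 9 of 16 in B belong to that protocol alone.

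**2. Numbers per contrast.** From section 2.2 there are 30 per cell and so 60 per pooled arm. With the 20% withdrawal stated there, 30 × 0.8 = 24 per cell and 60 × 0.8 = 48 per pooled arm. The sample size itself cannot be reproduced, because no effect size, SD or power is given. The dropout arithmetic fits both readings of the word group: 48/0.8 = 60 and 24/0.8 = 30.

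**3. What the pooled test shows if one protocol is inert.** These are assumptions, not figures from the article: a continuous outcome with SD 1 in every cell, effect d in group A, zero in group B, and a two-sided 0.05 level. The mean difference between pooled arms is then d/2, with standard error √(2/48) = 0.204.

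The unadjusted t-test does not use this standard error. Mixing means d and 0 in the active arm inflates the pooled SD to about √(1 + d²/8), so the test needs a larger difference to reach significance. For d = 0.8:

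- pooled SD ≈ √1.08 = 1.04
- critical difference ≈ 1.986 × 0.204 × 1.04 = 0.42
- true difference = 0.40, so P(p < 0.05) ≈ P(Z > (0.42 − 0.40)/0.204) ≈ 0.46

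Simulating the t-test agrees. The adjusted column is noncentral-t power at effect d/2 with SD 1.

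| d in group A | Pooled, unadjusted t-test | Pooled, adjusted for diagnosis group |
|---|---|---|
| 0.6 | 29% | 31% |
| 0.8 | 46% | 49% |
| 1.0 | 63% | 68% |

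**4. Contrast within one stratum.** For SGA versus CGA at d = 0.8 with 24 per cell, the noncentrality is 0.8/√(2/24) = 2.77 and the power is 77%, against 46% for the pooled unadjusted test.

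**5. Precision of the estimates proposed below, at 24 per cell.**

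- Stratum 95% CI half-width: t(46) × √(2/24) = 2.013 × 0.289 = 0.58 SD.
- Interaction standard error: √(4/24) = 0.408 SD. A difference of 0.8 SD between the two effects gives 0.8/0.408 = 1.96, or about 50% power. For 80% power the difference would have to be about 1.14 SD.

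**The case against.** The strongest reply is that the article nowhere specifies a pooled test. It randomises within each diagnosis, gives each stratum its own sham cell and names all four cells. Its sample-size sentence follows directly on the two diagnosis groups of 60. Section 4.3 also wants to describe the metabolic profile of each phenotype before and after its treatment. Two parallel sham comparisons are a natural reading, and naming contrasts is ordinary SAP content.

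Much of this stands. A reader might infer that one pooled p-value is fixed as the basis for validating both protocols; the text does not support that. SGA versus CGA and SGB versus CGB are valid randomised contrasts already. What remains lies in the article's own wording: it declares SG versus CG and a singular conclusion, beside a layout in which that contrast identifies neither protocol. The phenotype aim in section 4.3 is a before-and-after description of metabolic status, not a sham-controlled estimate by stratum.

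A second tempting inference is that the trial fails to test TCM-based point selection as it promised. It made no such promise. Its comparison is with sham, and the phrase about a TCM diagnostic can be read as saying where the points come from. The absence of a mismatched or untailored arm limits the conclusion and is no error in the sham comparison.

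Third, the illustration takes Protocol B as fully inert although it shares 7 needles with A. That is an extreme case, and the article gives no effect size to set against it.

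**Conclusion.** The point holds in a limited form. The declared SG versus CG contrast gives the average effect of two diagnosis-assigned protocols, and the singular validation aim in section 4.3 goes beyond what that average can carry.

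In the illustrative case, an inert protocol shares in a significant pooled result in roughly 29% to 63% of trials for d between 0.6 and 1.0. A working protocol with d = 0.8 is missed by the pooled test in just over half of trials (100% − 46% = 54%), against 23% (100% − 77%) in its own stratum. These sizes rest on the assumed effects, equal SDs, equal strata and 20% loss. That the average does not identify either protocol's effect depends on none of them.

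**What to change.** In sections 2.2, 3.3 and 4.3:

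1. Define SG versus CG as the average effect of diagnosis-assigned acupuncture versus sham, and analyse it stratified by TCM diagnosis group as a rule, since randomisation is done within those groups.
2. Report SGA versus CGA and SGB versus CGB, each with a 95% CI, and the treatment-by-diagnosis interaction, labelled low-powered.
3. Make an efficacy statement about Protocol A or Protocol B only from its own stratum.
4. Word the conclusion as a comparison with sham, and say that the trial gives no evidence on whether selecting points by TCM diagnosis adds to the effect.

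The cost is a change of wording and a few extra estimates per outcome, with no added patients or visits. The price is wide stratum intervals and a narrower claim. The choice should be written down before unblinding, so that nobody picks between overall and stratum results after seeing them.

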## 3. Results

The target of this study focuses on four types of parameters divided into primary, secondary, and exploratory outcomes. Primary outcomes refer to hormonal parameters, and secondary to anthropometric and metabolic parameters. Exploratory outcomes are related to quality-of-life analysis and will be performed using the Medical Outcomes Study 36-Item Short Form Health Survey [50], the Zung Self-Rating Anxiety Scale [51], and the Zung Self-Rating Depression Scale [52] (Table 3). All the questionnaires used are validated for Portuguese language. Outcome measures will be collected at baseline, 6 weeks, 12 weeks, and 6 months after the last acupuncture treatment (Table 2).

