**Figure 2 healthcare-10-01999-f002:**
[figure not shown]
Flowchart of the study period.

**Table 1 healthcare-10-01999-t001:** Rotterdam phenotypes for PCOS women with correspondent TCM phenotype.

Phenotype	Description
Rotterdam Phenotype A (classical PCOS) [46]	Hyperandrogenism + polycystic ovary morphology + ovulatory dysfunction—28.7%
TCM phenotype [47]	Spleen deficiency and phlegm stasis SP’s—32.27%
Rotterdam Phenotype B [46]	Hyperandrogenism + Ovulatory disfunction—19.0%
TCM phenotype [47]	Phlegm stasis and blood stasis—16.55%
Rotterdam Phenotype C [46]	Ovulatory disfunction + polycystic ovary morphology—37.3%
TCM phenotype [47]	Kidney deficiency and liver stasis—40.29%
Rotterdam Phenotype D [46]	Hyperandrogenism + polycystic ovary morphology—15.0%
TCM phenotype [47]	Kidney deficiency and blood stasis—10.89%

**Table 2 healthcare-10-01999-t002:** SPIRIT schedule of enrolment, interventions, and assessments.

	STUDY PERIOD														
	Enrolment	Allocation	Post-Allocation												Close-Out
TIMEPOINT	*−1 month*	0	* _W1_ *	* _W2_ *	* _W3_ *	* _W4_ *	* _W5_ *	* _W6_ *	* _W7_ *	* _W8_ *	* _W9_ *	* _W10_ *	* _W11_ *	* _W12_ *	*After 6 months*
ENROLMENT:															
Eligibility screen	X														
Informed consent	X														
Baseline assessments	X														
Allocation		X													
INTERVENTIONS:															
Active acupuncture															
		X	X	X	X		X		X		X		X	
Sham acupuncture															
		X	X	X	X		X		X		X		X	
ASSESSMENTS:															
*Diagnostic examination*	X														
*Primary and secondary outcomes*		X						X						X	X
*Life quality related questionnaires*	X	X						X						X	X

**Table 3 healthcare-10-01999-t003:** Primary, secondary, and exploratory outcomes that will be used in the study.

Primary	Secondary	Exploratory
**Hormonal Parameters**: Modified Ferriman-Gallwey score Ludwig visual score LH, mean (SD), mIU/mL FSH, mean (SD), mIU/mL LH/FSH Total free testosterone Androstenedione Progesterone, median (IQR), ng/mL Estradiol, median (IQR), pg/mL Sex hormone–binding globulin (SHBG), mean (SD), μg/mL Ovulation rate (%)	**Anthropometric parameters** Age (years) Height (cm) Weight (Kg) BMI (kg/m^2^) Waist circumference (cm) Waist Hip Ratio	**Quality-of-life scores**: Medical Outcomes Study 36-Item Short Form Health Survey Zung Self-Rating Anxiety Scale Zung Self-Rating Depression

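### SF-36 and Zung scales: the pre-treatment score is not fixed to one visit or one rule, and the planned tests leave it unused

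*Protocol article*

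**What the plan says.** Section 2.2 sets a general rule, "All baseline and follow-up measures should be obtained on a single day", and then an exception: "questionnaires may be spread between the screening and the baseline visit". It cites Table 2 for the exception and treats screening and baseline as two separate visits.

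The pre-treatment marks in Table 2 are:

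- Row "Baseline assessments": one mark, at −1 month, in the same column as the eligibility screen.
- Row "Primary and secondary outcomes": one mark, at time 0, the allocation column.
- Row "Life quality related questionnaires": two marks, at −1 month and at time 0.

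Section 3 names a single baseline followed by three later time points, and it classes the quality-of-life, anxiety and depression scores as exploratory. Section 3.3 plans chi-square tests, two-sample t-tests or rank sum tests, and an analysis of variance both between and within groups. It names no baseline covariate. Section 4.3 expects Zung scores to fall and SF-36 scores to rise after active acupuncture. For the biomarkers, it says that "it is expected to find a relative reduction of the biomarkers when comparing to baseline values".

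**The concern.** Text and table can be read together in three ways. Every woman completes every scale twice; different scales are completed at different visits; or each woman completes each scale once, at whichever visit suits. The article does not say which. Under the first reading there are two pre-treatment scores and no stated way to choose between them or combine them. Under the third, the date of the single score varies by up to a month from woman to woman.

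Two things are at stake. The before-after change that the article expects on these scales depends on which score is called baseline, and with no rule the choice can be made after the data are seen. In addition, the plan collects pre-treatment scores but names no analysis that uses them to sharpen the comparison between arms.

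**Working it through.** **Step 1: which outcomes are affected.** In the assessment rows of Table 2 the later marks fall at week 6, week 12 and close-out, which agrees with section 3. The first marks can therefore be trusted too. Pre-treatment marks: primary and secondary outcomes 1 (time 0); questionnaires 2 (−1 month and time 0). The ambiguity about the value itself is confined to the questionnaires.

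**Step 2: which comparison is affected.** Both columns precede treatment and apply alike to active and sham women. Whichever score is used, its expected value is the same in both arms. Within-group change has no such protection.

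**Step 3: what a fixed rule could gain.** The article gives no figure to reproduce, and no correlation. Assume equal variance at each visit (set to 1) and the same correlation rho between any two visits, with rho from 0.5 to 0.7.

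- Adjusting for one score leaves residual variance 1 − rho².
- The mean of two scores has variance (1 + rho)/2 and covariance rho with the follow-up score. Adjusting for it leaves 1 − rho²/((1 + rho)/2) = 1 − 2rho²/(1 + rho).

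| rho | No adjustment | One score | Mean of two | Ratio, two to one | Reduction | 1/ratio |
|---|---|---|---|---|---|---|
| 0.5 | 1.000 | 0.750 | 0.667 | 0.889 | 11% | 1.13 |
| 0.6 | 1.000 | 0.640 | 0.550 | 0.859 | 14% | 1.16 |
| 0.7 | 1.000 | 0.510 | 0.424 | 0.830 | 17% | 1.20 |

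At rho 0.6, the second score is worth about 16% more women for these scales, relative to adjusting for one.

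**Step 4: comparison with the tests in section 3.3.** That section does not say whether the two-sample tests use follow-up scores or changes.

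- On follow-up scores the variance is 1. Adjusting for one score removes 25%, 36% or 49% of it at rho 0.5, 0.6 and 0.7; adjusting for the mean of two removes 33%, 45% or 58%.
- On changes from one score the variance is 2(1 − rho) = 1.00, 0.80 or 0.60, which is above both adjusted figures in every row.

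Measured from unadjusted follow-up scores, most of the gain comes from adjusting at all; the second score adds the rest.

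**Step 5: sensitivity.** Two scores a month apart may correlate more strongly with each other than with a later score. With 0.7 between the two pre-treatment scores and 0.5 with follow-up, the mean of two leaves 1 − 2(0.25)/1.7 = 0.706. Against 0.750 for one score, that is a reduction of 6% (0.706/0.750 = 0.941). The 11% to 17% range therefore depends on equal correlations.

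**The case against.** The strongest reply is that section 2.2 declares the questionnaires an exception and cites Table 2 for it. The two marks may show no more than a permitted window, with each scale completed once. Text and table would then agree, and a second administration would be new work, not something already scheduled. This stands in part: a reader might infer a flat contradiction, and the documents do not show one. Even on that reading, however, the date of the score is not fixed.

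A second reply is that the choice of baseline value belongs in an analysis plan, and averaging two scores is an enhancement. This has weight for the choice of covariate. It has less for the schedule: which scale is completed at which visit is a matter of data collection, and no later plan can recover a score that was not taken.

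Three stronger readings are tempting, and the documents support none of them.

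- *The hormone baseline is also ambiguous.* Table 2 has one pre-treatment mark for primary and secondary outcomes, at time 0, and section 2.2 separates the baseline visit from screening. The row labelled "Baseline assessments" at −1 month competes with no outcome value.
- *Scores at −1 month are inflated, so the gain will be overstated.* No entry criterion in sections 2.3 or 2.4 uses a Zung or SF-36 score, so nobody is selected for an extreme value. Any drift is an assumption. On SF-36, moreover, worse health gives a lower score, so the direction would be reversed.
- *The treatment comparison is biased.* Both visits come before treatment in both arms.

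**Conclusion.** The point holds as a minor one, limited to the three exploratory questionnaires. Their pre-treatment value is either one score at a date that is not fixed or two scores without a rule, and this affects within-group change. No size can be put on that effect from the documents.

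The 11% to 17% measures something else: the precision available from a fixed two-score baseline compared with a one-score baseline. It rests on assumed equal variances, on equal correlations of 0.5 to 0.7 and on the use of a baseline-adjusted model, which section 3.3 does not name. It shrinks if the two pre-treatment scores correlate more strongly with each other than with follow-up.

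For primary and secondary outcomes, the mismatch is a row label and is clerical.

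**What to change.** 1. In section 2.2, delete the sentence that lets questionnaires be divided between the two visits. State instead that SF-36 and both Zung scales are given in full at −1 month and again at time 0, as Table 2 marks, with the time-0 set completed before allocation is revealed.
2. In section 3.3, state that the between-arm comparison of each scale is adjusted for the mean of its two pre-treatment scores, and that the same mean is the reference for within-group change.
3. In Table 2, reconcile the "Baseline assessments" row with the time-0 mark for primary and secondary outcomes, by moving or renaming it.

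The cost is protocol wording and one line of analysis. If the two marks were meant only as a window, there is also a second round of three questionnaires at a visit that already takes place. If that burden is unwelcome, naming one visit for all women and adjusting for that single score still removes the ambiguity; it gives up only the further 11% to 17%.
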